# Executive Summary

Tuberculosis transmission occurs predominantly indoors, often at home. We propose this trial to assess whether an improved and intensified household intervention for household contacts of TB cases prevents TB infection and disease in two different TB burden settings.

The recent ZAMSTAR study suggests that household contact tracing strategies for TB prevention may be more effective in preventing future TB infections and cases than untargeted community-based case finding approaches, which are also resource intensive and difficult to sustain. Since ZAMSTAR was completed there have been major strides in the diagnosis and prevention of TB – particularly in high HIV prevalence settings. Additionally, we have previously shown that household contacts of TB cases had substantially higher rates of undiagnosed TB compared to randomly selected households without an index TB case, and that a substantial proportion of culture-positive households contacts are asymptomatic. Moreover, we and others, have shown that using children as sentinel cases to direct active case finding also has a high yield of undiagnosed TB in household contacts. Finally, it appears that in high HIV prevalence areas, rates of TB in household contacts are high irrespective of whether contacts live in a TB “hot spot” or a far lower annual TB incidence setting.

We therefore propose a cluster randomised trial in three health districts in South Africa to investigate the effect of an intensified active case finding strategy with immediate initiation and of treatment and linkages to care for household contacts of index cases of TB diagnosed at two sites with different TB burdens. The three selected health districts are Matlosana, Mangaung and Capricorn, with annual TB incidence of 937/100,000; 686/100,000and 371/100,00 respectively. One thousand two hundred hospital- and/or clinic-diagnosed index TB cases of all ages will be recruited at each site. Their households will be randomly allocated to receive either an enhanced standard of care contact tracing strategy using referral letters with follow up phone calls, or an intensified household contact tracing and treatment support (IHCS) intervention comprising of:

1. Sputum Xpert and TB liquid culture for all household contacts capable of providing a sputum sample, irrespective of TB symptoms, with supported initiation and linkage to TB treatment in those with TB disease;
2. HIV testing with prompt initiation of both antiretrovirals and TB preventive treatment for HIV-infected contacts according to current South African guidelines,
3. Preventive therapy for tuberculin skin test-positive, HIV-negative **and** HIV-infected household contacts without active TB disease;
4. A three-month supportive follow-up visit to confirm treatment receipt, and assist those who have either not accessed care and treatment; or who have experienced problems with their treatment; or who have developed symptoms of TB in the interim.

**Objectives**:

Primary trial outcomes are:

1. Comparison between trial groups of TB FREE SURVIVAL from two months after randomisation – to the final ascertainment visit among all household members identified at baseline – a total of 13 months. We will measure this in two ways; firstly, including all cases of where TB was diagnosed or multi drug TB treatment started, irrespective of the diagnostic method used and secondly, including only those with a hard copy of a laboratory confirmation of TB.

*Secondary trial outcomes*

1. Comparison between trial groups of the proportion of TB cases with diagnostic delay (defined as number of days between onset of symptoms and diagnosis of anti-tuberculosis treatment) among household members identified at baseline and diagnosed with TB between baseline and month 15
2. Comparison between trial groups of the prevalence of TB infection measured by tuberculin skin test reactivity >10mm at month 15 among household children identified at baseline and aged under 14 years of age.
3. Comparison between trial groups of the prevalence (reported as a percentage of those tested) of previously undiagnosed and untreated HIV infection among household members identified at baseline and again at month 15.
4. Comparison between trial groups of the cumulative incidence of all-cause mortality among all household members identified at baseline between baseline and month 15.
5. Comparison between trial groups of the cumulative incidence of TB- and HIV-related non-traumatic mortality among all household members identified at baseline between baseline and month 15.
6. Estimation of the cost-effectiveness of the intensified housed TB and HIV case-finding and prevention activities compared to the enhanced standard of care from a societal perspective. This will include comparisons of household costs and of quality of life of household members in the IHF and enhanced standard of care arms.

*Exploratory outcomes*

1. Cohort analysis of the incidence of bacteriologically-confirmed, and all-forms of tuberculosis among intervention group household members receiving and not receiving isoniazid preventive therapy, stratified by HIV serostatus.
2. Cohort analysis of the proportion of household members in the intervention group with previously undiagnosed HIV infection identified at baseline who successfully initiate antiretroviral therapy by month 15.
3. Estimation of the fraction of TB transmission to household members attributable to household exposure to TB index cases by analysis of whole genome sequences of sputum TB isolates (*Subject to further funding being secured)*
4. To quantify catastrophic costs linked to a new TB and/or HIV diagnosis or death due to TB and/or HIV of a household member (estimated at baseline prior to the intervention being implemented).

Developmental Outcome: This project will support and train the newly established Department of Internal Medicine at the University of Limpopo Medical School in Polokwane to conduct clinical research, as we will include both the Capricorn Health District in Limpopo Province and the Matlosana sub-district in North West Province. In addition, we will ensure that at least three South African masters students and at least one PhD student use data from this study for their research projects.

Background

*TB Epidemiology in high HIV prevalence settings*

Tuberculosis remains a public health priority, and is now the leading cause of death from an infectious disease worldwide. In sub-Saharan Africa, TB incidence rates initially skyrocketed, driven principally by extremely high prevalence rates of HIV infection. South Africa is the country with the largest number of people living with HIV worldwide, and has experienced extremely high rates of TB incidence, prevalence and mortality.

The new End-TB Strategy calls for bold action to eliminate tuberculosis as a public health issue by 2035. Central to the End-TB strategy is a recognition that intensified action, driven by innovate research, is required to find and treat all cases of tuberculosis, and to identify high-impact strategies to limit transmission to vulnerable individuals. Moreover, high out of pocket costs of care-seeking and treatment have proved to be catastrophic for many people living in poverty. Interventions that can effectively make TB treatment equitable, affordable and accessible are required.

*Intensified case-finding approaches for tuberculosis need to be evaulated*

Contact tracing of index TB cases (sometimes known as “sentinel” or “source” cases) has been advocated as a key part of TB control for many years (Grzybowski, 1975; World Health Organization, 2012; Rieder, 2003) because it facilitates early identification of symptomatic and infectious linked cases, and allows individuals with TB infection to receive preventive treatment. Although, World Health Organization (WHO) and National Guidelines in South Africa recommend household contact tracing, the 2012 WHO guidelines have not been prioritized or widely implemented in South Africa (or indeed many other high TB burden countries) because of the current very low quality of available evidence for effectiveness, and the requirement to reallocate resources in settings that are struggling to identify and treat TB patients presenting with symptoms (Claassens, 2013).

Recently, the groundbreaking ZAMSTAR community randomized trial in Zambia and South Africa (Ayles, 2013) has shown that a household contact tracing intervention was superior to an untargeted community TB case finding intervention, albeit with borderline significant benefit on two primary community-wide outcome measures: reduction of new TB infections in young children; and reduction of prevalence of TB in the communities which received contact tracing. The ZAMSTAR household contact tracing intervention comprised of: Identification of target households through adult index TB cases; symptom screening of household contacts to identify individuals with presumptive TB for further investigation; screening of symptomatic individuals using sputum smear microscopy. To date, the ZAMSTAR study team has not reported on process and outcome indicators of the household intervention, such as: newly diagnosed with TB and/or HIV who accessed the care and prevention services; or the number of times the entire household was offered TB symptom screening; or the proportion of patients who should have received TB preventive treatment, and/or ART, who actually received it. Additionally, the symptom-based, sputum smear screening strategy used in ZAMSTAR to identify and investigate TB suspects likely missed household contacts with prevalent infectious TB, thereby limiting the effectiveness household intervention.

Our studies in households of adult TB cases in two different South African settings where HIV prevalence is high, suggests that a substantial proportion of household contacts who have sputum cultures positive for *M tuberculosis* do not report symptoms and, under the ZAMSTAR strategy, would ***not*** be identified by symptom screening (Shapiro, 2013). Moreover, unpublished data from the Vhembe health district in Limpopo (a South African TB “cold spot”) showed that household contact tracing identified similar rates of undiagnosed TB in household contacts as in the TB hotspot of Matlosana, and also, many of them were asymptomatic. (Little K, et al; submitted).

Mathematical modelling work emphasizes that failure to detect asymptomatic or subclinical TB limits the impact on community TB transmission and that earlier identification and prompt treatment results in improved population-level TB control (Dowdy, 2013). Moreover, sputum smear has insufficient sensitivity when used in contact tracing, where a large proportion of contacts are HIV infected, and active TB is identified earlier and is likely to be paucibacillary.

In the intervening period since the final ZAMSTAR prevalence survey in 2010, there have been considerable advances in TB diagnosis, and prevention. Routine TB diagnostics have improved markedly with the widespread scale-up of the Xpert MTB/Rif molecular TB diagnostic platform (Boehme CC, 2010) (and more recently with a newer, apparently more sensitive version the Xpert Ultra not yet available for use). Xpert MTB/Rif reduces diagnostic delay and results in earlier TB treatment initiation (Theron G, 2014); TB preventive treatment guidelines for HIV-infected individuals have evolved to recommend long-term, more effective regimens (Samandari 2011, Martinson 2011), that when co-administered with antiretroviral therapy (ART), are safe and reduce mortality and TB disease (TEMPRANO ANRS 12136 Study Group 2015, Rangaka 2014). The CD4 threshold for initiating ART has been raised to 500 cells/mm3 and likely will be redundant when the test-and-treat strategy is implemented; and first line ART regimens have been simplified to single daily dosing with fixed-dose combination tablets. Moreover, children diagnosed with TB are increasingly being recognized as important sentinel cases for rapid identification of an infectious household TB case (Puryear,2013; Lala, 2014). Finally our data shows that HIV-seronegative household contacts in a high burden setting in the year after a household contact tracing intervention have annual TB incidence of 700/100,000 (van Schalkwyk, 2014) – suggesting preventive treatment against TB should be offered to HIV seronegative adults and older children in contact with a case, although this is not currently part of guidelines for preventive treatment in South Africa.

**We therefore hypothesise that a household intervention that actively includes these recent improvements will improve TB free survival** **and decrease the prevalence of new TB infections in children**.

# Overall aim

The overall aim of the study is to investigate the effect on household contacts of a TB case of an intensified household contact tracing and treatment support (IHCS) for household contacts of index adult and paediatric cases of TB diagnosed in clinics and hospitals in two sites with markedly different TB burdens.

# Objectives

**Primary objectives:**

1. To assess the impact of the intensified household case-finding strategy on:
   1. TB free survival among all household contacts
   2. Prevalence of TB infection in household contacts under 14 years of age.
2. To assess the cost effectiveness of IHCS compared to the enhanced standard of care.

**Secondary objectives:**

1. To assess the effectiveness of isoniazid preventive treatment on new cases of TB in HIV-seronegative individuals who are tuberculin skin test positive.
2. To compare the yield and costs of IHCS versus standard of care in identifying undiagnosed cases of TB and undiagnosed or untreated HIV
3. To compare rates of linkage to TB treatment between participants identified with TB through IHCS and standard of care
4. To explore perceptions and acceptability of doing home visits with household members

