**Follow-up household visit (1week after baseline household visit)**
Xpert MTB results and results of laboratory HIV testing (and CD4 counts and HbA1C as appropriate) will be communicated to participants by study staff including registered nurses at a follow-up household visit approximately one-week after the baseline assessment is completed. Participants with microbiologically-confirmed tuberculosis or diagnosed with HIV will be supported to attend their nearest local primary care clinic to register for ongoing care and treatment.

Participants who are older than 5 years of age or test HIV-negative and whose sputum tests are negative for TB and whose tuberculin skin test is negative will be dispensed the first month of IPT by study nurse and then referred for ongoing preventive treatment at their local clinics with a clear referral letter that includes all results. Additionally all those participants who are less than 5 years of age or are HIV-positive and sputum tests are negative for TB will be dispensed the first month of isoniazid preventive therapy by study nurses, Linkage to care will be confirmed by collection of referral cards at study facilities by study staff. Home tracing to encourage re-entry to care will be undertaken on three occasions for participants who do not attend clinics within 2 weeks of referral.

Should any liquid TB culture be resulted positive after this visit, a visit will be made to the few anticipated households from where this result was taken to inform the patient and refer him/her for TB treatment.

| **Age of household member** | **HIV status** | **TST Required** | **Active TB disease** | **TB HH contact** | **IPT initiated** | **Study procedure** |
| --- | --- | --- | --- | --- | --- | --- |
| Child < 5 years | POSITIVE on ART or not | NO | NO | YES | YES | Initiate 1 month IPT |
| Child ≥5 years, adult or adolescent | POSITIVE on ART or not | NO | NO | YES | YES | Initiate 1 month IPT |
| Child < 5 years | NEG | NO | NO | YES | YES | Initiate 1 month IPT |
| Child ≥5 years, adult or adolescent | NEG | YES | NO | YES | YES | Initiate 1 month IPT |

Table 1. IPT initiation for household contacts without TB symptoms

*Final intervention household visit (3 months after baseline household visit)*

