All intervention households will be visited once at approximately three months after the initial assessment. This visit will be offered because our previous data suggests that a significant proportion of household members with either TB, or HIV, diagnosed at the baseline household visit, do not access care or treatment. Patients not accessing TB treatment, ART or IPT care will be reassessed and assisted to start appropriate treatment, with study staff attempting to overcome access barriers identified by this group. In addition, we will reassess whether those with hypertension or those diagnosed with type 2 diabetes mellitus were started on appropriate therapy and are at this visit controlled or have a plan for future care. Household members requiring other assistance or care will receive supported access to their local health facility or to the Department of Social Development to access social grants. Moreover, at this visit a TB symptom screen on all available household members not on TB treatment will be done, with investigation of those with symptoms, using Xpert and TB culture. We will not visit the household again to interview household members not present at this single final intervention visit.

All visits will be recorded including the number and level of staff members and the purpose and duration of the visit.

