**Non-intervention group (Enhanced standard of care)**
After index cases have been allocated to the non-intervention group at their health facility,, a careful census of the demographic characteristics of each household member will be recorded from the index case. A single contact will be made with the non-intervention index cases at the time of randomisation. Each recruited index case allocated to the non-intervention group will be provided with a referral letter for every household member they identify, and will be requested to give the pre-printed referral letter to each person in their household. The referral letter will contain information about tuberculosis and HIV and will provide recommendation to household members, that they should be screened for TB and HIV, with details of local health facilities where screening and further care (if required) may be accessed. Additionally, the referral letter will contain guidance for health providers, including recommendations that TB screening, HIV testing and further care and prevention services (including ART and TB preventive therapy as required) should be offered as per National guidelines because the individual was exposed to a likely infectious case of TB.

After approximately a week, Study Research Assistants will make a follow up call to the index case or the caregiver of the index case to assess if the referral letters were given to household members and to confirm that any ill household members have accessed their local health facility. If they have been unable to do this, advice on locations of clinics, and other assistance will be provided telephonically. No further contact will be had with non-intervention index cases of households till the final outcome visit.

**All households: final outcome assessment visit**We will conduct an outcome household visit to all households, irrespective of their study allocation at 15 months after the recruitment of the index case and initial first visit to the household and 12 months after the second follow up visit. Although the study is unblinded, we will attempt to limit research field staff’s knowledge of initial allocation; and in training for and the conduct of the final outcome assessment we will not refer to households as intervention or non-intervention households.

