Finding households of index cases can be time consuming, and ideally non-intervention households should be as similar to intervention households as possible. To try and ensure that non-intervention households are not visited by teams who have been searching for a household for longer periods than intervention households where locations are known, 2-6 months prior to the final outcome visit – if resources permit - we will send a study staff team member to locate the non-intervention houses and reintroduce the study to at least one household member. Apart from confirming the address using the what3word App, no data will be recorded.

At the final outcome visit, Research Assistants will revisit all households 1) trace all household participants, ascertain vital status and brief verbal autopsies for those who have died; 2) record episodes of TB and HIV diagnosis and when they occurred, treatment and other hospitalizations from verbal report and inspection of patient-held records; and 3) investigate participants with symptoms of TB (any of: cough, fever, weight loss, night sweats) by collecting sputum for smear microscopy, sputum culture and Xpert; and 4) encourage and offer repeat HIV testing to participants negative or not previously tested at baseline; and 5) conduct a prevalence survey for latent TB infection by testing all children under 14 years old with the tuberculin skin test, read at 48-72 hours later as described previously; 6) a livestock survey will also be done on a sub-sample of 300 households (150 households per site) assessing exposure to domestic pets and livestock and consumption of raw milk.

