## Health economics and costing procedures

All costing and economic evaluations will be primarily from the perspective of the health care system to enhance comparability with other studies. However, estimates of household costs of illness and deaths will also be included in certain cost effectiveness measures to reflect a societal perspective. The analysis will also explore the magnitude of household costs, potential for catastrophic costs of HIV and TB, and implications for universal access.

We will use a direct costing approach to assess incremental costs of the ICHF intervention in achieving the primary objective. Costs of diagnostic tests will be obtained from actual expenditures and price lists. Staff costs will be based on public sector remuneration scales for relevant staff, combined with observations, recording time use and services delivered, both to distinguish services from each other and to quantify, cost and exclude research specific activities. Travel costs will be based on logbooks and similar cost allocation approaches. Where any other substantial costs are identified and cannot be directly costed, e.g. management overheads, these will be estimated using step down methods. Household members will be asked at interview about direct and indirect costs (e.g. lost income) of illness and accessing healthcare, and about effect on various household asset holdings (appliances, cellphones etc.) to explore dissaving and potential for catastrophic costs.

The principal cost effectiveness indicators will be incremental costs per person diagnosed with HIV and/or TB, and importantly cost per person linked to HIV and/or TB care through the ACF intervention in each setting, and cost per incident TB case and death avoided, as these could inform immediate, large-scale policy choices. Further indicators such as estimated incremental cost per life year saved or per TB treatment completion will be generated if the frequency and profile of reported clinical outcomes support this. In addition, we will measure health-related quality of life of household members using the EuroQol EQ-5D adjusted for Southern Africa (Maheswaran et al. 2016)

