# Study Definitions

**Households:** Physical dwelling structures comprising of all rooms under a contiguous roofed area linked by doorways or windows through which air can pass or potentially can pass.

**Household members:** All individuals who shared household airspace for lengthy periods – either slept overnight at least once, or shared at least two meals in the same household as the index case - in the 14 days prior to the index case’s diagnosis of TB

**Incident bacteriologically-confirmed TB** will be defined by a household contact who has documented evidence of at least one of any of the following: sputum smear positive for acid-fast bacilli; or culture with growth of Mycobacterium tuberculosis confirmed on speciation; or positive Xpert MTB/Rif result; or histology or cytology suggestive of TB, regardless of whether TB treatment was initiated. We will restrict incident cases to those diagnosed on a specimen taken at least 2 months after the initial baseline household contact.

**Incident bacteriologically unconfirmed TB** will be defined by a household contact without bacteriologically-confirmed TB but who has at least one of the following: TB treatment registers, or patient held TB treatment cards indicate TB treatment was initiated; or either died or was discharged from hospital with a diagnosis of TB without laboratory confirmation.

**All forms of TB** will be defined in individuals with either bacteriologically-confirmed, or bacteriologically-unconfirmed TB.

**Prevalent *Mycobacterium tuberculosis infection*** will be defined by the presence of skin induration reaction measured to be >10mm using technique recommended by the International Union Against Tuberculosis and Lung Disease at 48-72 hours after subdermal injection of 2 TU in 0.1 ml PPD RT23/Tween 80 in children younger than 7 years of age.

**Prevalent previously undiagnosed HIV infection** will be defined by household members who, at month 15 assessment, test positive for HIV using a serial rapid diagnostic test algorithm infection, having reported never previously tested positive for HIV.

**Prevalent previously undiagnosed and untreated HIV infection** will be defined by household members who, at month 15 assessment, test positive for HIV using a serial rapid diagnostic test algorithm infection and report not currently taking antiretroviral therapy.

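### Secondary objective 3 compares linkage to TB treatment among cases ascertained differently in each arm, so control linkage is probably biased upward and the comparison could reverse

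*Protocol*

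**What the plan says.** The objective (Protocol, Secondary objectives, item 3) is "To compare rates of linkage to TB treatment between participants identified with TB through IHCS and standard of care". The protocol describes how TB becomes known, and how linkage is observed, separately for each arm.

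- **Intervention, detection.** The Executive Summary lists "Sputum Xpert and TB liquid culture for all household contacts capable of providing a sputum sample, irrespective of TB symptoms". Under Sputum Collection, the sample is taken before symptoms are asked about.
- **Intervention, linkage.** Under the one-week follow-up visit: "Linkage to care will be confirmed by collection of referral cards at study facilities by study staff". Home tracing and a three-month visit follow. The three-month visit is justified by earlier data suggesting that "a significant proportion of household members with either TB, or HIV, diagnosed at the baseline household visit, do not access care or treatment".
- **Control.** The index case receives referral letters for household members and one telephone call after about a week. Then: "No further contact will be had with non-intervention index cases of households till the final outcome visit".
- **Final visit, both arms.** Staff "record episodes of TB and HIV diagnosis and when they occurred, treatment and other hospitalizations from verbal report and inspection of patient-held records". Participants with symptoms are sputum-tested.
- **Case definitions.** In Study Definitions, one route to unconfirmed TB is that "TB treatment registers, or patient held TB treatment cards indicate TB treatment was initiated". Confirmed TB counts whether or not treatment began, and a hospital death or discharge with a TB diagnosis also counts.

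Health economics and costing procedures names, among the principal indicators, "importantly cost per person linked to HIV and/or TB care through the ACF intervention in each setting".

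**The concern.** A linkage proportion has treatment starts as its numerator and known cases as its denominator. The comparison is fair only if treated and untreated cases are equally likely to become known in each arm.

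In the intervention arm, a screen-detected case is known before treatment is an issue, and failure to start is actively looked for. In the control arm, someone who started treatment usually has a card and an episode to report. Someone who was diagnosed and never started, or never received the result, may have neither. Entry to the control denominator then depends partly on the outcome.

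The groups also differ in kind. The Background says that a substantial proportion of culture-positive contacts report no symptoms. Universal testing brings these people into the intervention denominator, while many would go undiagnosed under standard of care. Randomisation does not protect a comparison of two groups selected in this way.

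At stake is the reading of a secondary objective: an intervention that links a larger share of its cases could appear to link a smaller one. The primary outcome is not affected.

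**Working it through.** The protocol states no linkage rate, sample size or power for this objective, so there is no figure to reproduce. The check asks how far unequal capture could move the comparison.

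**Inputs.** All are assumed; none is in the protocol.
- Lc, Li: true linkage among diagnosed cases, control (0.60 to 0.80) and intervention (0.85 to 0.95).
- a: probability that a treated control case becomes known, set at 0.95.
- u: probability that a diagnosed but untreated control case becomes known, from 0 to 0.95.
- Intervention cases are taken as captured equally whether treated or not, because study testing comes before treatment. This is an approximation, since later episodes in that arm are also learned by report.

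**Step 1: observed control linkage.**

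Observed = Lc·a / [Lc·a + (1 − Lc)·u]

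Example with Lc = 0.70 and u = 0.25: 0.665 / (0.665 + 0.075) = 89.9%.

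| u | True 60% | True 70% | True 80% |
|---|---|---|---|
| 0 | 100% | 100% | 100% |
| 0.05 | 96.6% | 97.8% | 98.7% |
| 0.10 | 93.4% | 95.7% | 97.4% |
| 0.25 | 85.1% | 89.9% | 93.8% |
| 0.50 | 74.0% | 81.6% | 88.4% |
| 0.75 | 65.5% | 74.7% | 83.5% |
| 0.95 | 60% | 70% | 80% |

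The bias is upward whenever u is below a and disappears when they are equal.

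**Step 2: when the order reverses.** Setting observed control linkage equal to Li gives the threshold:

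u/a < Lc(1 − Li) / [Li(1 − Lc)]

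- 85% v 70%: 0.70 × 0.15 / (0.85 × 0.30) = 0.105 / 0.255 = 0.41
- 85% v 60%: 0.60 × 0.15 / (0.85 × 0.40) = 0.090 / 0.340 = 0.26
- 85% v 80%: 0.80 × 0.15 / (0.85 × 0.20) = 0.120 / 0.170 = 0.71
- 95% v 70%: 0.70 × 0.05 / (0.95 × 0.30) = 0.035 / 0.285 = 0.12

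A small true advantage reverses under mild differential capture; a large one needs severe differential capture.

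**Step 3: a denominator that does not depend on being identified.** Let D be the proportion of listed members who are diagnosed. Treatment starts observed per listed member are then D·L·a. The term u drops out, so failure to learn of untreated cases no longer affects the result. What remains is capture of treated cases, which is alike across arms only if the same source is used in both.

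**The case against.** The strongest reply is that treatment is not the only way into the control denominator. Confirmed TB counts whether treated or not, hospital diagnoses count, verbal report covers diagnosis as well as treatment, and symptomatic members of both arms are sputum-tested at month 15. This stands. A reader might infer that control linkage is close to 100% by construction, and the documents do not support that. In the table, with true linkage of 70%, about 96% or more needs u of 0.10 or less, and nothing in the protocol fixes u there. These routes reduce the problem without removing it. Confirmed TB needs documentation, and the stated month-15 sources are verbal report and patient-held records; laboratory lists are described only for finding index cases. Cases found at month 15 are found by the study, and no later visit is described at which their linkage could be seen. Counting them as unlinked would lower the observed proportion, which is one more reason why the size is unknown.

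Second, the treatment-based definition is written for incident TB and applies to both arms, and the protocol does not name it as the denominator for this objective. That is fair. Linkage may be defined in an analysis plan that is not shown, and its absence here is not the point. The difficulty is that the objective itself restricts the comparison to identified cases.

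Third, the statement about contacts not accessing care describes earlier data and is the reason for adding support. It does not predict non-linkage in this trial. Correct, and the working does not use it as an input.

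Fourth, a reader might infer that the cost per person linked inherits the bias. It is built on a count of people linked, so this proportion does not directly bias it.

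Fifth, linkage is conventionally conditional on diagnosis, and objective 2 covers yield. Reading the two together helps, but it does not correct a denominator selected on the outcome.

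**Conclusion.** The concern holds in a limited form. Followed as written, secondary objective 3 gives a non-randomised comparison of differently ascertained groups. Observed control linkage is probably biased upward, to a degree that the protocol does not allow anyone to estimate. Reversal of the true order is possible: below a capture ratio of about 0.41 for 85% v 70%, 0.71 for 85% v 80%, and 0.12 for 95% v 70%. These thresholds rest on assumed linkage values and on equal capture of treated and untreated cases in the intervention arm. The direction rests on untreated control cases being harder to learn of than treated ones, which the month-15 sources make likely but do not prove. The point warrants a change to how one secondary objective is analysed and no more than that.

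**What to change.** 1. Report the proportion of identified cases who start treatment descriptively, by arm, with the difference in ascertainment stated beside it and no between-arm test.
2. For the randomised comparison, use the number of household members started on TB treatment from randomisation to month 2 per 1,000 members listed at baseline. Take treatment starts and dates from the month-15 interview and patient-held records in both arms, and show by arm how many listed members have no final-visit information.

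The window should close at month 2 because the primary outcome, TB-free survival, is counted from two months after randomisation. A treatment start after that point is a primary-outcome failure, so a window running to month 15 would credit as linkage the incident TB that the trial aims to prevent.

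The cost is rewording one objective. No new data are needed, since the final visit already records episodes, dates and treatment in both arms. There are four drawbacks. The measure combines detection with linkage and no longer isolates the linkage step. It rests on fewer events. It relies on recall of dates more than a year earlier where no card is held. It also leaves out starts prompted by the three-month intervention visit, which the descriptive report in item 1 should show.
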